### Reporting of adverse events

Participants will be asked to contact the study site immediately in the event of any serious adverse event. All adverse events will be recorded and closely monitored until resolution, stabilisation, or until it has been shown that the study medication or treatment is not the cause. The Chief Investigator shall be informed immediately of any serious adverse events and shall determine seriousness and causality in conjunction with any treating medical practitioners.

In the event of a pregnancy occurring in a trial participant or the partner of a trial participant monitoring shall occur during the pregnancy and after delivery to ascertain any trial related adverse events in the mother or the offspring. Where it is the partner of a trial participant consent will be obtained for this observation from both the partner and her medical practitioner.

All serious adverse events will be recorded and reported to the MHRA and REC as part of the annual reports. SUSARs will be reported within the statutory timeframes to the MHRA and REC as stated below. The Chief Investigator shall be responsible for all adverse event reporting.

## SUSARs

**A serious adverse event that is either sudden in its onset, unexpected in its severity and seriousness or not a known side effect of the IMP *and* related or suspected to be related to the IMP is classed as Suspected Unexpected Serious Adverse Reaction and requires expedited reporting as per the clinical trials regulations.**

**All serious adverse events that fall or are suspected to fall within these criteria shall be treated as a SUSAR until deemed otherwise.**

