### Maintenance of randomisation codes and procedures for breaking code

Study medications (active and placebo) will be produced to MHRA standards by Catalent Pharma Solutions.

Investigators may identify the treatment for each participant in the event of a medical emergency when treatment is dependent on knowledge of the actual drug received. This will be by means of opening a sealed envelope containing the details of drug allocation to each participant.

If the treatment code for a participant is broken, an urgent meeting of the study personnel (Independent trials pharmacist, [name] and [name], [name] or [name]). The date and reason(s) for breaking the code will be recorded. The participant will continue follow up unless consent is withdrawn.

When the un-blinding is part of managing an SAE, unblinding will be reported with the SAE, however, in cases where un-blinding was not associated with an SAE, such actions will be reported in a timely manner. The default will be to use the same timeline requirements for investigator reporting of SAEs (notification of Sponsor immediately as practicable by phone or fax, followed by a written narrative of the event within 48 hours).

At the end of the study, randomisation and code break envelopes will be returned to pharmacy for disposal.

Treatment allocations will be identified by revealing the randomisation code at the end of the study.

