# ADVERSE EVENTS

### Definitions

An adverse event is any unfavourable and unintended sign, symptom, syndrome or illness that develops or worsens during the period of observation in the study.

An AE does include a / an:

1. exacerbation of a pre-existing illness.

2. increase in frequency or intensity of a pre-existing episodic event or condition.

3. condition detected or diagnosed after medicinal product administration even though it may have been present prior to the start of the study.

4. continuous persistent disease or symptoms present at baseline that worsen following the start of the study.

An AE does not include a / an:

1. medical or surgical procedure (e.g., surgery, endoscopy, tooth extraction, transfusion); but the condition that lead to the procedure is an AE.

2. pre-existing disease or conditions present or detected at the start of the study that did not worsen.

3. situations where an untoward medical occurrence has not occurred (e.g., hospitalisations for cosmetic elective surgery, social and / or convenience admissions).

4. disease or disorder being studied or sign or symptom associated with the disease or disorder unless more severe than expected for the participant’s condition.

5. overdose of concurrent medication without any signs or symptoms.

A Serious Adverse Event (SAE) is any adverse event occurring following study mandated procedures, having received the IMP or placebo that results in any of the following outcomes:

1. Death

2. A life-threatening adverse event

3. Inpatient hospitalisation or prolongation of existing hospitalisation

4. A disability / incapacity

5. A congenital anomaly in the offspring of a participant

Important medical events that may not result in death, be life-threatening, or require hospitalisation may be considered a serious adverse event when, based upon appropriate medical judgment, they may jeopardize the patient or participant and may require medical or surgical intervention to prevent one of the outcomes listed in this definition

All adverse events will be assessed for seriousness, expectedness and causality:

A distinction is drawn between serious and severe AEs. Severity is a measure of intensity whereas seriousness is defined using the criteria above. Hence, a severe AE need not necessarily be serious.

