### Causality

**Not related or improbable**: a clinical event including laboratory test abnormality with temporal relationship to trial treatment administration which makes a causal relationship incompatible or for which other drugs, chemicals or disease provide a plausible explanation**.** This will be counted as “unrelated” for notification purposes.

**Possible**: a clinical event, including laboratory test abnormality, with temporal relationship to trial treatment administration which makes a causal relationship a reasonable possibility, but which could also be explained by other drugs, chemicals or concurrent disease. This will be counted as “related” for notification purposes.

**Probable**: a clinical event, including laboratory test abnormality, with temporal relationship to trial treatment administration which makes a causal relationship a reasonable possibility, and is unlikely to be due to other drugs, chemicals or concurrent disease. This will be counted as “related” for notification purposes.

**Definite**: a clinical event, including laboratory test abnormality, with temporal relationship to trial treatment administration which makes a causal relationship a reasonable possibility, and which can definitely not be attributed to other causes. This will be counted as “related” for notification purposes.

An AE whose causal relationship to the study IMP is assessed by the Chief Investigator as “possible”, “probable”, or “definite” is an Adverse Drug Reaction.

With regard to the criteria above, medical and scientific judgment shall be used in deciding whether prompt reporting is appropriate in that situation.

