**The event shall be reported immediately of knowledge of its occurrence to the Chief Investigator.**

**The Chief Investigator will:**

- Assess the event for seriousness, expectedness and relatedness to the study IMP
- Take appropriate medical action, which may include halting the trial and inform the Sponsor of such action
- If the event is deemed a SUSAR, shall, within seven days, complete the CIOMS form and send to the MHRA.
- Shall inform the REC using the reporting form found on the NRES web page within 7 days of knowledge of the event
- Shall, within a further eight days send any follow-up information and reports to the MHRA and REC.
- Make any amendments as required to the study protocol and inform the ethics and regulatory authorities as required

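### The SUSAR definition counts sudden onset as a criterion and joins severity to seriousness with 'and', so it does not match the expectedness assessment the protocol requires

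*Protocol*

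**What the plan says.** The section SUSARs gives the operative definition. A serious adverse event qualifies if it is "either sudden in its onset, unexpected in its severity and seriousness or not a known side effect of the IMP" and is, in addition, "related or suspected to be related to the IMP is classed as Suspected Unexpected Serious Adverse Reaction and requires expedited reporting". A default for doubtful cases follows: "All serious adverse events that fall or are suspected to fall within these criteria shall be treated as a SUSAR until deemed otherwise".

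The list of the Chief Investigator's actions in the same section begins with a separate step: "Assess the event for seriousness, expectedness and relatedness to the study IMP". Only if the event is then judged to be a SUSAR does the form go to the MHRA within seven days; the REC is told in the same time.

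Under Adverse Events, the Definitions section also requires every adverse event to be assessed for expectedness, and it distinguishes two terms: "Severity is a measure of intensity whereas seriousness is defined using the criteria above". The section Reporting of adverse events sets the route for serious events in general: "All serious adverse events will be recorded and reported to the MHRA and REC as part of the annual reports". The sections Description and Known Side Effects refer to an SmPC supplied with the protocol, but the SUSAR definition does not mention it.

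**The concern.** A SUSAR is by name an unexpected reaction, so its definition should turn on whether the event departs from what is known about the product. Two features of the sentence work against that.

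- **Onset.** Speed of onset says nothing about whether a reaction was expected, yet it stands as a criterion.
- **Severity and seriousness.** The protocol itself says these are different properties. Joining them with 'and' means that, read literally, a reaction must be unexpected in both. A reaction already known to be serious cannot meet that condition however intense it is.

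At stake is which events reach the regulator and the ethics committee quickly. An event wrongly left out waits for the annual report. An event wrongly included adds expected reactions to the expedited reports. Two people applying the text faithfully could also classify the same event differently.

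**Working it through.** No figure in the plan bears on this, so the check is logical. Take a serious event already judged related, and record four yes/no attributes:

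- S: onset is sudden
- V: severity is unexpected
- R: seriousness is unexpected
- U: not a known side effect

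The sentence can be parsed in three ways:

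- Reading 1 (three alternatives, 'and' taken literally): S or (V and R) or U
- Reading 2 (three alternatives, 'and' taken loosely): S or V or R or U
- Reading 3 (the comma taken as a joint condition): (S and V and R) or U

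The yardstick is what the category's name implies, unexpected in some respect: V or R or U.

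| Related serious event | Reading 1 | Reading 2 | Reading 3 | Yardstick |
|---|---|---|---|---|
| Known, sudden, nothing unexpected | SUSAR | SUSAR | no | no |
| Known, gradual, only severity unexpected | no | SUSAR | no | SUSAR |
| Known, gradual, severity and seriousness both unexpected | SUSAR | SUSAR | no | SUSAR |
| Not a known side effect | SUSAR | SUSAR | SUSAR | SUSAR |

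Over all 2 × 2 × 2 × 2 = 16 combinations, reading 1 departs from the yardstick in 3, reading 2 in 1 and reading 3 in 5. These are counts of logical cases, not frequencies of events.

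- Reading 1, the most natural literal one, has both faults: the first row is included and the second is left out.
- Reading 2 catches the second row but still includes the first. Its only error is over-reporting.
- Reading 3 excludes the first row but misses the second, and also the third.

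No reading matches the yardstick. The default for doubtful cases does not close the gap, because it refers back to the same criteria: an event plainly outside them is not suspected to fall within them.

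Against the neighbouring sections: Definitions and the Chief Investigator's action list both call for an expectedness assessment, but neither says what expected means or against which document. The SUSAR sentence is the only place that supplies criteria, and one of them is not about expectedness.

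**The case against.** The strongest reply is that the sentence does not operate alone.

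- The Chief Investigator assesses expectedness before the form is sent, and an event is held as a SUSAR only until judged otherwise. A sudden but expected event could therefore be screened out. This stands in part: such an event meets the definition, but the documents do not establish that it would always be sent.
- The Causality section says that "medical and scientific judgment shall be used in deciding whether prompt reporting is appropriate in that situation", and expedited reporting is tied to the clinical trials regulations. This leaves room for sensible practice but sets no standard for expectedness, so it does not repair the wording.
- The Chief Investigator is told of every serious event at once, and the DMEC has access to all study data. This limits the consequence inside the trial. It does not change when the MHRA and REC hear of the event.

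A reader might infer that every gradual, known reaction of exceptional severity escapes expedited reporting while every sudden expected one is expedited. The text does not support that. Both results occur together only under reading 1, and only where the gradual reaction's seriousness was already expected. A known, usually non-serious reaction that turns both serious and unusually severe, each unexpectedly, is caught on that reading.

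A reader might also infer that reports are prepared blind, so that placebo events are filed against pioglitazone. The code-break section lets investigators identify treatment "in the event of a medical emergency when treatment is dependent on knowledge of the actual drug received", but it does not say how SUSAR reports are prepared. It also foresees unblinding as part of managing a serious event. The inference rests on silence.

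**Conclusion.** The definition is wrong as written. It contains a criterion unrelated to expectedness, it merges two properties the protocol separates, and it does not match the expectedness assessment required in two other places. No parsing makes it correct.

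The size can be given only as time. A gradual, known, related reaction that is unexpected in severity alone moves, on readings 1 and 3, from the seven-day route to the annual reports, a wait of up to about a year at the outside. How many such events would occur cannot be estimated: the documents give no expected rate of serious events for the 50 participants planned on pioglitazone, and the SmPC is not at hand. For the same reason no particular organ or reaction can be cited as an example; the conditions named in the exclusion criteria are bars to entry, not a list of known reactions with their severity.

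The conclusion assumes that the written definition governs classification and that judgment does not override it. Sample size, type I error and the efficacy analysis are not affected.

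**What to change.** In the section SUSARs, delete the onset criterion and replace the remaining criteria with one test: a SUSAR is a serious adverse event, related or suspected to be related to the IMP, whose nature or severity is not consistent with the SmPC that accompanies the protocol. State that the expectedness assessments in Definitions and in the Chief Investigator's action list use the same test and the same SmPC, so that the three places agree. It would help to add whether a listed reaction that becomes serious in a way the SmPC does not describe counts as unexpected; on the literal reading it is now covered only if its severity is unexpected too, its onset is sudden, or it is not a known side effect.

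The cost is a one-sentence replacement with two cross-references. No visit, treatment rule, endpoint or analysis changes.

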**The event shall be reported immediately of knowledge of its occurrence to the Chief Investigator.**

**The Chief Investigator will:**

- Assess the event for seriousness, expectedness and relatedness to the study IMP
- Take appropriate medical action, which may include halting the trial and inform the Sponsor of such action
- If the event is deemed a SUSAR, shall, within seven days, complete the CIOMS form and send to the MHRA.
- Shall inform the REC using the reporting form found on the NRES web page within 7 days of knowledge of the event
- Shall, within a further eight days send any follow-up information and reports to the MHRA and REC.
- Make any amendments as required to the study protocol and inform the ethics and regulatory authorities as required

### Participant removal from the study due to adverse events

Any participant who experiences an adverse event may be withdrawn from the study at the discretion of the Investigator.

# ETHICAL AND REGULATORY ASPECTS

## ETHICS COMMITTEE AND REGULATORY APPROVALS

The trial will not be initiated before the protocol, informed consent forms and participant and GP information sheets have received approval / favourable opinion from the Medicines and Healthcare products Regulatory Agency (MHRA), Research Ethics Committee (REC), and the respective National Health Service (NHS) Research & Development (R&D) department. Should a protocol amendment be made that requires REC approval, the changes in the protocol will not be instituted until the amendment and revised informed consent forms and participant and GP information sheets (if appropriate) have been reviewed and received approval / favourable opinion from the REC and R&D departments. A protocol amendment intended to eliminate an apparent immediate hazard to participants may be implemented immediately providing that the MHRA, R&D and REC are notified as soon as possible and an approval is requested. Minor protocol amendments only for logistical or administrative changes may be implemented immediately; and the REC will be informed.

The trial will be conducted in accordance with the ethical principles that have their origin in the Declaration of Helsinki, 1996; the principles of Good Clinical Practice, in accordance with the Medicines for Human Use Regulations, Statutory Instrument 2004, 1031 and its subsequent amendments and the Department of Health Research Governance Framework for Health and Social care, 2005.

## INFORMED CONSENT AND PARTICIPANT INFORMATION

The process for obtaining participant informed consent or assent and parent / guardian informed consent will be in accordance with the REC guidance, and Good Clinical Practice (GCP) and any other regulatory requirements that might be introduced. The investigator or their nominee and the participant or other legally authorised representative shall both sign and date the Informed Consent Form before the person can participate in the study.

The participant will receive a copy of the signed and dated forms and the original will be retained in the Trial Master File. A second copy will be filed in the participant’s medical notes and a signed and dated note made in the notes that informed consent was obtained for the trial.

The decision regarding participation in the study is entirely voluntary. The investigator or their nominee shall emphasize to them that consent regarding study participation may be withdrawn at any time without penalty or affecting the quality or quantity of their future medical care, or loss of benefits to which the participant is otherwise entitled. No trial-specific interventions will be done before informed consent has been obtained.

The investigator will inform the participant of any relevant information that becomes available during the course of the study, and will discuss with them, whether they wish to continue with the study. If applicable they will be asked to sign revised consent forms.

If the Informed Consent Form is amended during the study, the investigator shall follow all applicable regulatory requirements pertaining to approval of the amended Informed Consent Form by the REC and use of the amended form (including for ongoing participants).

## RECORDS

### Drug accountability

Drug supplies will be kept in a secure, limited access storage area under the storage conditions specified by Pharmacy.

The investigator and the local site pharmacist shall maintain records of the study drug’s delivery to the pharmacy, an inventory at the site, the distribution to each participant, and the return to the pharmacy or alternative disposition of unused study drugs. These records will include dates, quantities received, batch / serial numbers, expiration dates, and the unique code numbers (patient trial number) assigned to the trial participant. Investigators and /or the local site pharmacists will maintain records that document adequately that the participants were provided with the correct study medication. These records will be part of each patient’s Case Report Form (CRF). All study medication packs and bottles received by the pharmacy shall be accounted for.

### Case Report Forms

Each participant will be assigned a trial identity code number, allocated at randomisation, for use on CRFs other trial documents and the electronic database. The documents and database will also use their initials (of first and last names separated by a hyphen or a middle name initial when available) and date of birth (dd/mm/yy). Data entry will occur directly into a web-based electronic CRF (eCRF) set-up and maintained by Nottingham Clinical Trials Unit. The eCRF includes data encryption for personal information as well as an audit trail to log all online data entry and any changes in the data fields.

CRFs will be treated as confidential documents and held securely in accordance with regulations. The investigator will make a separate confidential record of the participant’s name, date of birth, local hospital number or NHS number, and Participant Trial Number (the Trial Recruitment Log), to permit identification of all participants enrolled in the trial, in case additional follow-up is required.

CRFs shall be restricted to those personnel approved by the Chief or local Principal Investigator and recorded on the ‘Trial Delegation Log.’

All paper forms shall be filled in using black ballpoint pen. Errors shall be lined out but not obliterated by using correction fluid and the correction inserted, initialled and dated.

The Chief or local Principal Investigator shall sign a declaration ensuring accuracy of data recorded in the CRF.

### Source documents

Source documents shall be filed at the investigator’s site and may include but are not limited to, consent forms, current medical records, laboratory results and pharmacy records. A CRF may also completely serve as its own source data. Only trial staff as listed on the Delegation Log shall have access to trial documentation other than the regulatory requirements listed below.

### Direct access to source data / documents

The CRF and all source documents, including progress notes and copies of laboratory and medical test results shall made be available at all times for review by the Chief Investigator, Sponsor’s designee and inspection by relevant regulatory authorities (e.g., MHRA, EMEA).

## DATA PROTECTION

All trial staff and investigators will endeavour to protect the rights of the trial’s participants to privacy and informed consent, and will adhere to the Data Protection Act, 1998. The CRF will only collect the minimum required information for the purposes of the trial. CRFs will be held securely, in a locked room, or locked cupboard or cabinet. Access to the information will be limited to the trial staff and investigators and relevant regulatory authorities (see above). Computer held data including the trial database will be held securely and password protected. All data will be stored on a secure dedicated web server. Access will be restricted by user identifiers and passwords (encrypted using a one way encryption method).

Information about the trial in the participant’s medical records / hospital notes will be treated confidentially in the same way as all other confidential medical information.

Electronic data will be backed up every 24 hours to both local and remote media in encrypted format.

